## Abstract

**Background:**

Increasing evidence links gut microbiota composition to neurological disorders, including Alzheimer’s disease (AD), through the gut-brain axis. Microbial metabolites such as lipopolysaccharide (LPS) and butyrate are associated with AD progression. Among modifiable factors, diet plays a central role in shaping gut microbiota and may influence disease-related microbial patterns. Personalized nutrition based on individual microbiota profiles offers a promising strategy to modulate these biomarkers. This protocol describes a study designed to develop a personalized dietary supplement for patients with AD by integrating microbiota, clinical, and dietary data using artificial intelligence (AI) and network analysis. A secondary objective is to assess in a pilot study the short-term effects of the supplement on microbiota composition, function, and plasma metabolomics to identify modifiable biomarkers.

**Design:**

This two-phase study will begin with baseline data collection from 60 patients with AD and 60 healthy controls. AI and network-based analyses will identify dietary and microbial variables predictive of disease status. Based on these findings, a personalized supplement will be formulated using dietary components—such as fibers, polyphenols, or fatty acids—targeting microbial taxa and metabolic pathways associated with AD. In the second phase, 60 patients with AD will be randomized (1:1) to receive either the personalized supplement or a standard product for 3 months. Effects on microbial taxa, LPS, short-chain fatty acids (SCFAs), and plasma metabolites will be evaluated before and after the intervention.

**Methods:**

Participants will undergo assessments of lifestyle factors, including diet and physical activity, as well as measurements of blood LPS and fecal SCFAs. Machine learning and network analyses will explore links among microbiota, diet, and clinical features. Predictive variables will guide supplement design. The intervention will evaluate changes in LPS, butyrate, and microbial markers. Plasma metabolomic profiles will also be analyzed. Data integration using AI and network approaches will help identify biomarkers and assess intervention outcomes.

**Discussion:**

Combining AI and network analysis in microbiota research supports the development of personalized nutrition strategies in AD. This approach may modulate disease-related microbiota and systemic markers, contributing to innovative therapeutic tools and advancing both Alzheimer’s care and nutritional science.

**Clinical trial registration:**

ClinicalTrials.gov, identifier NCT06199193.

## Introduction

1

Alzheimer’s disease (AD) is an irreversible degeneration of the brain that causes disorders of memory, cognition, personality, and other functions, ultimately leading to death due to complete cessation of brain activity. It is estimated that there are 50 million people worldwide living with dementia, and two-thirds of them suffer from AD. By 2030, without new discoveries, this number is expected to rise to nearly 75 million patients (1). The gut microbiota plays a crucial role in the bidirectional communication between the gut and the brain, and accumulating evidence suggests its involvement in AD pathophysiology (2). For instance, elevated levels of bacterial lipopolysaccharides (LPS) have been positively associated with cerebral amyloidosis, while higher production of short-chain fatty acids (SCFAs), particularly butyrate, by the gut microbiota has been linked to reduced amyloid deposition (3).

Currently, there is no effective treatment for AD, but studies indicate that following a healthy diet, such as the Mediterranean diet (MD), and engaging in physical activity may delay the symptoms of the disease (4, 5). Adherence to Mediterranean and Mediterranean-DASH Intervention for Neurodegenerative Delay (MIND) diets has been associated with reduced risk of cognitive decline in observational studies (6, 7). However, the first randomized controlled trial of the MIND diet (8) did not show significant differences in cognitive outcomes compared to a healthy control diet. Recent meta-analyses continue to support potential protective effects of Mediterranean-type diets but emphasize heterogeneity across populations and study designs (9). Nutritional supplementation has also been widely investigated. A recent meta-analysis of omega-3 fatty acids, docosahexaenoic acid (DHA), eicosapentaenoic acid (EPA), and Souvenaid^®^ concluded that these interventions may modestly attenuate cognitive decline, with benefits most consistently observed in Clinical Dementia Rating scores, though overall findings remain heterogeneous and not statistically conclusive (10). Evidence from randomized controlled trials indicates that physical exercise is the most consistently beneficial lifestyle intervention, improving quality of life, mobility, and certain cognitive domains, even though effects on biomarkers remain inconclusive (11). Combined interventions, particularly those integrating exercise with cognitive stimulation or other modalities, appear promising but yield heterogeneous results and require further validation (11). Overall, while observational studies consistently suggest protective effects of diet and lifestyle factors on AD onset, randomized trials in patients indicate only modest benefits on disease progression, particularly with nutritional supplements and exercise.

Since many of these lifestyle and nutritional interventions are known to modulate the gut microbiota, it has been suggested that targeting microbial composition and activity through diet could represent a novel or adjuvant therapeutic strategy in AD (12). In this regard, foods or dietary patterns that reinforce the intestinal barrier to reduce the translocation of LPS into the bloodstream (and ultimately to the brain), and/or reduce populations of Gram-negative bacteria (carriers of LPS), and/or increase butyrate production by the microbiota, could serve as adjuvant treatments for patients with AD (13). However, these patients are often highly resistant to lifestyle changes, showing poor adherence to new dietary habits, and the responsibility for implementing these changes often falls on caregivers, increasing their physical and emotional burden (14). For these reasons, the use of dietary supplements providing essential and beneficial components of the diet could be an effective strategy as an adjuvant treatment for these individuals (15).

There is increasing evidence that physiological responses to diets or dietary components depend on individual characteristics (sex, genetics, age), dietary habits, and, in part, on the composition of the gut microbiota (16, 17). Therefore, for dietary interventions to be successful, they must be adapted by considering various individual factors such as dietary habits, personal characteristics, and microbiota composition (18). To study the interactions among individual characteristics, microbiota composition, and diet, and to integrate all this data to understand changes in human physiology, new computational approaches such as artificial intelligence (AI) are increasingly being used (19). These methods help us understand complex interactions, treating the individual as a system in order to predict physiological changes resulting from external modifications such as diet. In fact, some of these computational methods, including machine learning (ML) algorithms, have already been used to design personalized diets and improve health-related parameters (16, 20, 21). By combining these concepts, personalized microbiota-based nutrition, along with computational tools such as ML and network analysis, is beginning to be used to predict clinical phenotypes, opening the door to new advances in the prevention and treatment of diseases through this approach (18). Although most of our current knowledge comes from experimental studies, it should be possible to develop mechanistic-based mathematical models to assist in designing intervention strategies (22).

However, despite increasing evidence linking gut microbiota, diet, and AD, there are currently no personalized dietary supplements specifically designed for patients with AD that integrate individual clinical, dietary, and microbiota data. Existing nutritional interventions are largely generic and do not account for patient heterogeneity or the mechanistic pathways connecting diet, microbiota, and AD-related biomarkers. This gap highlights the need for the present protocol, which aims to address these limitations by proposing a data-driven framework for supplement development and preliminary validation.

This protocol describes a study whose aim is to investigate the feasibility of designing personalized nutritional supplements for patients with AD based on their sex, age, medical history, dietary habits, physical activity, and gut microbiota, applying AI and bioinformatics tools through a data-driven approach. In this context, study success, referred to as “greater efficacy” is defined as promoting a microbiota with a higher presence of health-associated species, reducing microbial taxa related to AD, and modifying AD-related biomarkers. The use of a combination of predictive and causal approaches (including network analysis) to integrate and simultaneously analyze patient clinical data, dietary and exercise habits, and microbiota profiles will allow us to identify dietary variables that should be modified to induce changes in factors related to AD prevention (e.g., butyrate) or progression (e.g., LPS and microbiota markers). The overarching goal is to determine whether such a tailored supplement would exhibit greater efficacy than currently available products. A medical food product designed to support brain health in individuals with AD will be used as a comparator. Finally, the study aims to identify new AD-related markers modified by the designed supplement using a metabolomic approach.

The findings may lead to the development of new, customized nutritional products by food and pharmaceutical companies, offering substantial socio-economic benefits. Moreover, the study’s multidisciplinary approach could advance both Alzheimer’s care and the science of personalized nutrition, providing a model for future research and clinical applications.

## Methods

2

### Participants

2.1

Patients diagnosed with AD at the Dementia Unit of “Hospital Clínico Universitario Virgen de la Arrixaca” (HCUVA) in Murcia and the Neurodegenerative Diseases and Movement Disorders Unit of “Hospital Universitario Puerta de Hierro” (HUPHM) in Madrid (Spain), who meet the inclusion criteria and none of the exclusion criteria, and who are willing to participate in the study, will be recruited. Caregivers may also participate as control subjects. Recruitment will be conducted by neurologists from the research team. Potential participants will be identified among current patients of the Dementia Unit and the Neurodegenerative Diseases Unit. Participants will be recruited from HCUVA and HUPHM. Inclusion criteria will be men and women aged 60 to 85 years with AD at Global Deterioration Scale (GDS) stage 3, confirmed by cerebrospinal fluid (CSF) biomarkers. Availability of a study partner who has regular contact with the participant, can accompany them to study visits as needed, assists with supplement intake and study procedures, and can provide collateral information. Healthy control group, healthy caregivers of patients with AD may be included as control subjects if they meet the eligibility criteria. Exclusion criteria include the presence of other diseases that may interfere with sample results, such as gastrointestinal disorders (e.g., ulcerative colitis, Crohn’s disease), autoimmune diseases, chronic antibiotic use or antibiotic treatment within the past 3 months, chronic treatment with immunosuppressants, corticosteroids or immunomodulators, a history of cancer treated with chemotherapy in the past 5 years, intellectual disability, or acquired brain injury.

### Interventions

2.2

The study consists of three main stages (Figure 1). At baseline (*T* = 0), both healthy subjects and patients will undergo characterization, including demographic data, physical characteristics (age, sex, BMI, etc.), frailty (Clinical Frailty Scale for Accumulation of Deficits, CFS), malnutrition (Mini Nutritional Assessment questionnaire, MNA), clinical data (biochemistry, hematology, apolipoprotein E (APOE) genotyping, inflammatory markers, etc.), diet, physical activity (International Physical Activity Questionnaire for the Elderly, IPAQ-E), gut microbiota (diversity, composition, and community interactions), blood LPS and butyrate levels, as well as comorbidities and medications. All the collected variables will be subjected to network and predictive analyses (e.g., random forest) to examine interactions between variables and identify modifiable predictors of AD through dietary intervention. In the second stage, a personalized supplement will be designed based on the characteristics of patients with AD, though patients themselves will not be involved in this phase. In the third stage, a randomized, parallel-group nutritional intervention trial will be conducted to compare the “*ad hoc*” designed supplement with a standard nutritional supplement commonly used in patients with AD. The interval between baseline characterization (*T* = 0) and the beginning of the intervention (*T* = 2) will vary depending on recruitment, sequencing, and data processing times. The intervention will start as soon as possible after completion of these analyses, in order to maximize the relevance of the baseline analyses. During this period, participants will continue their usual medical care without changes. The intervention will last 3 months (pre-intervention: *T* = 2; post-intervention: *T* = 3) to evaluate the supplement’s effectiveness in modulating the microbiota, LPS levels, and butyrate production. Additionally, a metabolomic analysis will be conducted to identify new biomarkers related to the supplement’s effects on the disease.

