### Allocation

2.5

For the nutritional intervention study, patients with AD will be randomly assigned to two groups (*n* = 30 each) using the free randomization software OxMar (26). Randomization will not be stratified by study site. However, the study site will be included as a covariate in the statistical models to control for its potential effect as a confounding variable. The control group will receive a standard nutritional supplement commonly used in patients with AD (Souvenaid^®^, Nutricia, Madrid, Spain), and dietary recommendations will be provided if their usual intake does not meet the established nutritional goals for this population. The intervention group will receive the newly designed supplement, along with tailored dietary recommendations. The group assignment will be performed by the team of neurologists. Supplement blinding in terms of format, flavor, odor, etc., is not planned in this study. Supplements will be labeled as either “A” or “B,” and participants will be informed that they are taking a supplement but will not know whether it is the standard or the “*ad hoc*” formulation. To eliminate bias, the researchers conducting the experiments and performing the analyses will remain blinded to group allocation. Baseline demographic and clinical information will be collected for participants who discontinue the study, along with available data on health status, adverse events, and primary efficacy outcomes.

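### With Souvenaid as the only control and unequal dietary advice, the arm contrast can show greater efficacy over Souvenaid only and does not identify the supplement's own effect

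*Protocol article*

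**What the plan says.** The protocol article words the question of the intervention stage in several ways.

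- **The supplement's own effect.** In the Abstract (Background), a secondary objective is to "assess in a pilot study the short-term effects of the supplement on microbiota composition, function, and plasma metabolomics". Section 2.2 (Interventions) says the 3 months serve to evaluate the supplement's "effectiveness in modulating the microbiota, LPS levels, and butyrate production". Section 2.3 (Outcomes) makes the change in gut microbiota of patients before and after the intervention part of the primary outcome, without mention of a between-arm difference.
- **Superiority.** The Introduction states: "The overarching goal is to determine whether such a tailored supplement would exhibit greater efficacy than currently available products". Greater efficacy is defined there as "promoting a microbiota with a higher presence of health-associated species, reducing microbial taxa related to AD, and modifying AD-related biomarkers". The next sentence but one reads: "A medical food product designed to support brain health in individuals with AD will be used as a comparator".
- **The control.** Section 2.5 (Allocation) says: "The control group will receive a standard nutritional supplement commonly used in patients with AD", and names it as Souvenaid. Control patients get dietary recommendations only if their intake falls short of nutritional goals. The intervention arm gets the new supplement and tailored recommendations. No placebo, untreated or advice-only arm is planned.
- **The analysis.** Section 2.21 (Statistical analysis) takes personalised supplement versus control as the main fixed effect.
- **What is known of the comparator.** The Introduction lists Souvenaid among nutritional supplements that have been studied and then says that "many of these lifestyle and nutritional interventions are known to modulate the gut microbiota". It does not say this of Souvenaid by name.

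**The concern.** The stated questions are wider than the randomised contrast. An effect of the supplement itself needs a reference that is inert on the markers, or one whose effect is known. The control here is an active product whose effect on microbiota, LPS and butyrate is not given, and dietary advice also differs between the arms. Superiority over existing products in general would need more than one product.

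What is at stake is what may be concluded. On the present wording, a null arm difference could be reported as no effect of the supplement, and a positive one as its own effect or as superiority over the market. Neither follows. Section 2.4 (Sample size calculation) also says the pilot will estimate effect sizes and provide data to power a later definitive trial. If those are relative to Souvenaid but labelled as effects of the supplement, a later trial with a different control would be sized on the wrong quantity.

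**Working it through.** **The plan's own figure.** Section 2.4 gives mean abundances of one genus of 0.77 (AD) and 0.26 (healthy) and a pooled SD of 0.6533.

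- Effect size: (0.77 − 0.26) / 0.6533 = 0.7807 (stated 0.7806).
- n per group = 2 × (1.960 + 0.8416)² / 0.7807² = 25.76, which rounds up to 26 (stated 25).
- Dropout: 25 × 1.2 = 30 per arm, as stated.

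The figure reproduces to within one patient per group. It is a patient-versus-healthy difference. No effect of the new supplement or of Souvenaid enters it, so it says nothing about the size of the present problem.

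**What each contrast estimates.** For one marker over T=2 to T=3, let D be change over time without intervention, N and S the effects of the new supplement and of Souvenaid, and A_t and A_c the average effects of tailored and of conditional advice. Additivity is assumed for illustration.

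- Change in the new arm: D + N + A_t
- Change in the control arm: D + S + A_c
- Arm contrast: (N − S) + (A_t − A_c)

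Randomisation removes D from the contrast. It does not remove S or the difference in advice. The contrast differs from N by −S + (A_t − A_c), and the documents give neither term. If the advice effects were equal and S lay anywhere from −0.3 to +0.3 SD (an assumed range), the contrast would miss N by +0.3 to −0.3 SD.

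**Readings of the same result**, with equal advice effects:

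| Arm contrast | Compatible with |
|---|---|
| Zero | N = S = 0 (neither works); N = S > 0 (both work equally) |
| Positive | N > S ≥ 0; or N = 0 and S < 0 |

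**The before/after change.** Within the new arm it is D + N + A_t. D covers drift and regression to the mean, and no concurrent arm without an active product estimates it. The healthy group is not randomised and takes no part in this stage.

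**Superiority.** The contrast does address whether the new package does better than Souvenaid with conditional advice. It carries no information on any other product.

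**Data already planned.** LPS, SCFAs and bile acids are measured at T=0, T=2 and T=3 (section 2.3). Microbiota is measured at T=0 (section 2.2) and before and after the intervention (section 2.3). The T=0 value could serve as a second baseline covariate. With correlations a (T=0, T=2), b (T=0, T=3) and c (T=2, T=3), the residual variance is 1 − (b² + c² − 2abc)/(1 − a²), against 1 − c² with T=2 alone. All correlations below are assumptions.

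| a = b | c | Two baselines | T=2 only | Reduction |
|---|---|---|---|---|
| 0.3 | 0.3 | 0.862 | 0.910 | 5% |
| 0.5 | 0.5 | 0.667 | 0.750 | 11% |
| 0.7 | 0.7 | 0.424 | 0.510 | 17% |
| 0.2 | 0.3 | 0.890 | 0.910 | 2% |
| 0.3 | 0.5 | 0.725 | 0.750 | 3% |
| 0.5 | 0.7 | 0.480 | 0.510 | 6% |

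The first three rows take all visits as equally correlated. The last three allow for a weaker link to T=0, which is likelier with a long, variable gap. This is a gain in precision only and does nothing for the choice of comparator.

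**The case against.** An active comparator is a legitimate choice, and much of the text is already comparative. Section 2.2 says the third stage compares the designed supplement with a standard one, and the Introduction announces a single medical food as comparator right after stating the goal. The stage is a pilot, and the Discussion says it is not meant to give definitive outcomes. Effect sizes relative to Souvenaid are the right input if the later trial keeps that control. All of this stands. It limits the point to what may be concluded and does not make the design invalid.

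Three stronger readings are tempting, and the documents do not support them.

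- A reader might infer that the trial answers neither question. It does answer greater efficacy for the named comparator, as a comparison of packages.
- A reader might infer that the protocol itself says Souvenaid modulates the microbiota. It says so of many lifestyle and nutritional interventions, not all, and names no product. Activity on these markers is possible but not stated. The point needs only that the effect is unknown.
- A reader might want to put the harm as lost power. With 25 per arm and a two-sided 0.05 t-test, 0.7806 SD gives 77%, and taking off 0.1, 0.2 or 0.3 SD gives 65%, 52% or 38%. The arithmetic is right, but 0.78 is a patient-versus-healthy difference and the shifts are invented. These figures are not evidence of the size of the problem.

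Pilot status does not dispose of what remains. The aims still speak of effectiveness and greater efficacy, the primary outcome still includes an uncontrolled before/after change, and effect estimates are to be carried forward.

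**Conclusion.** The point holds in a limited form. The randomised contrast is valid for the new supplement plus tailored advice against Souvenaid plus conditional advice. It supports a statement on greater efficacy over Souvenaid only. It does not identify the supplement's own effect on microbiota, LPS or butyrate, and the within-arm change does not fill that gap.

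The size of the discrepancy cannot be given from the documents. It is the unknown Souvenaid effect combined with the unknown difference in the effect of advice, and either sign is possible. The conclusion rests on the two arms and their advice as described in section 2.5 and on no assumption about what Souvenaid does. It should be corrected because it changes what the trial may claim, at almost no cost.

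**What to change.** Leave the arms and the sample size as they are.

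1. In the Abstract, the Introduction and sections 2.2 and 2.3, state the randomised question as the between-arm difference in 3-month change for the supplement-plus-advice package versus Souvenaid with conditional advice. In the Introduction, replace the plural reference to existing products with the named comparator.
2. State that a null contrast does not show absence of effect.
3. Label within-arm before/after changes as uncontrolled. In section 2.4, label the effect sizes passed to a later trial as relative to Souvenaid, or as uncontrolled where they come from one arm.
4. Optional: report the T=0 to T=2 change descriptively as a non-randomised reference and state its limits. The interval varies, T=0 data select the target markers (so regression to the mean can enter here), and usual medical care is unchanged but diet is not held fixed.
5. Optional: add the T=0 value beside T=2 as a covariate where both exist. On the assumed correlations above, this lowers residual variance by about 5 to 17% if visits are equally correlated, and by about 2 to 6% if T=0 is more weakly related.

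Cost: items 1 to 3 are wording and a narrower claim. Item 4 is one descriptive analysis of data already planned. Item 5 costs one degree of freedom per model.
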